**Inclusion and Exclusion Criteria**

**Phase 3: Full Trial**

There are 2 tiers of inclusion and exclusion criteria. The first tier is eligibility criteria for the longitudinal study which will be determined through a brief screening assessment. The second tier is eligibility for the RCT which will be assessed during the baseline survey.

Inclusion criteria for longitudinal study include:

1. 18-55 years old
2. HIV Risk Behavior:

3a. Injected drugs more than 3 times in the past week OR

3b. Smoked crack in the past 6 months AND had 1 of the following sex risks in the past 6 months:

- - - 2 or more sex partners
    - Had a sex partner who injected drugs
    - Had a sex partner who smoked crack
    - Had a sex partner who was HIV+

1. Willingness to attend group sessions

Exclusion criteria for longitudinal study include:

1. Enrolled in another HIV behavioral intervention or depression study in past the 3 years
2. Enrolled in another Lighthouse study in past the 5 years
3. Enrolled in the formative research (Phase 1) or pilot (Phase 2) of the current project.

The 2^nd^ tier will be for randomization into the RCT. These criteria will be assessed during the baseline survey.

Inclusion criteria for the RCT include:

1. Met inclusion criteria for longitudinal study (see above)
2. Have depressive symptoms as determined by CESD scores 16 or greater at baseline assessment

Exclusion Criteria:

1. Severe levels of depression as determined by CESD score ≤40
2. Symptoms of mental illness that require treatment (i.e., actively manic, actively psychotic, DSM IV Axis II Cluster B such as histrionic, borderline, anti-social)

Individuals who are excluded based on mental illness will be given referrals to local agencies that provide mental health services.

In addition, individuals who are disruptive to the group will be removed from the group session and provided with other referrals.

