**RESEARCH PLAN**

#### **PI: [name] Study Title:** The Impact of Neighborhoods, Networks, and Depression on Drug Users’ HIV Risk (NND)

**Sponsor’s Protocol # *1071***

**Research Question:**

This study will implement and evaluate a small group, randomized controlled, phase II intervention to reduce depressive symptoms and HIV risk behaviors among inner city drug users. The intervention will include elements of cognitive behavioral therapy (CBT) for depression among impoverished individuals, emphasizing depressive cognitions and behaviors theorized to be associated with depression and with HIV risk behaviors among mildly to moderately depressed drug users. CBT has been found to be a highly successful, cost-effective approach to depression treatment for low-income minorities, and may be an important approach to reducing HIV risk behaviors among depressed inner city drug users.

This study will also longitudinally examine active drug users’ social and environmental pathways to depression and subsequent HIV risk behaviors. Specifically, we will examine hypothesized mediating/moderating effects of neighborhood characteristics, social network factors, and individual level factors on depressive symptoms and HIV risk behaviors.

This study will include multiple phases: (1) Phase 1: Formative Research to gather information from the target population for materials and curriculum for the intervention, (2) Phase 2: Piloting of project protocols and procedures, and (3) Phase 3: Delivery of the full intervention and data collection. At this time, we are only requesting permission for Phase 1: Formative Research and Phase 2: Piloting.

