This study will delineate social environmental pathways that lead to depressive symptoms and HIV risk behaviors. Understanding these dynamics is critical for developing sustainable multilevel interventions for HIV prevention. Another aim of this study is to test a behavioral intervention that targets a key pathway to HIV risk behaviors, namely the path between depressive symptoms and HIV risk behaviors. Although it is often acknowledged that social environmental characteristics are important risk factors, few interventions have assessed how social environmental factors may facilitate or impede behavior change. In this study, we expect that individuals who live in more stressful neighborhoods will be more likely to relapse into depression and sexual and drug-related HIV risk behaviors. We also expect that support network factors, such as emotional support, may ameliorate the negative impact of neighborhood stressors. The proposed intervention will target individuals who have mild to moderate levels of depressive symptoms.

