**Population:**

**Phase 3: Full Trial**

Approximately 500 crack smokers and 500 injectors will be recruited to participate in the longitudinal component of the study (i.e. baseline and follow-up assessments) Of these, approximately 250 crack smokers and 250 injectors with CES-D scores ≥16 will be randomly assigned to either the depression intervention or control condition.

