# Power calculations

# The main outcomes of interest are changes in injection and sexual risk behavior and in level of depressive symptoms. A sample size of 200 in each group is assumed for comparisons of sex risk behaviors and depressive symptoms after two years of follow-up with a 10% attrition rate per year. Only half of the sample will be IDUs, and it is assumed that there will be a sample size of 100 per group with the same attrition rates. There will be approximately 50 cohorts (25 intervention cohorts and 25 control cohorts) of with approximately 8 members with complete data at the end of the two years. The power was calculated for an assessment of intervention effectiveness at the end of the study, when sample sizes will be smallest and thus underestimates likely power for comparisons made earlier in the study. Power calculations were done using NCSS/PASS software. Based on the SHIELD study (IRB# H.30.00.07.17.A), we would expect an average CES-D score of 26.7 and variance of 8.3, given the selection methods proposed in the present study. We estimated power with a 2-sided test, setting the alpha at 0.05, with a total sample size of 400. We expect a small amount of correlation due to intervention group (0.02 in the SHIELD Study). A difference between the two groups post intervention on mean CES-D score of 2.0 provides sufficient statistical power.

|  | **Intercluster correlation** | | |
| --- | --- | --- | --- |
| **Difference in mean CES-D score** | 0.00 | 0.02 | 0.05 |
|  | **Power** | | |
| 2.0 | 0.92 | 0.88 | 0.83 |
| 3.0 | 0.99 | 0.99 | 0.99 |
| 4.0 | 1.00 | 1.00 | 1.00 |

Prior studies suggest a larger effect size for intervention effects on injection as compared to sexual risk behaviors. Consequently, despite the smaller sample size for injection risk comparisons, we expect analyses of the two outcomes to have similar statistical power. We based estimates of expected reduction in risk behaviors on the SHIELD study, creating composite scores for injection risk behavior (needle and cooker sharing and frequency of injecting) and sexual risk behavior (9 risk behaviors). The injection risk score had a mean of 11.6 (SD=4.5). The sex risk composite score had a mean of 1.9 (SD=1.8).

|  | Intercluster correlation | | |  | Intercluster correlation | | |
| --- | --- | --- | --- | --- | --- | --- | --- |
| Diff. in mean injection risk score | 0.00 | 0.02 | 0.05 | Diff. in mean sex risk score | 0.00 | 0.02 | 0.05 |

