**Methods of Intervention**

*Methods for Dealing with Adverse Events*

Study staff will be trained to identify and manage adverse events (e.g., participants becoming mentally distressed, carrying weapons, using drugs and alcohol, or becoming ill). Study staff have attended trainings given by the Maryland AIDS Administration, Baltimore Crisis Response (BCR), and the House of Ruth, a local domestic violence program.

The Lighthouse has established collaborative relationships with a variety of local resources such as local drug treatment, mental health, and other service providers who have facilitated referrals for past Lighthouse study participants. We also maintain an extensive community resource database that is updated several times throughout the year. We work closely with the Johns Hopkins Hospital and the Baltimore Crisis Response (BCRI), a community-based mental health service provider. Individuals who report very high levels of depressive symptoms will be referred to the BCRI. If participants report suicidal ideation or otherwise indicate psychiatric crisis, the interviewer will notify [name] (Co-Investigator) or [name] (Project Director) who will facilitate his/her call to the BCRI for evaluation. Upon participant request, BCRI will send a counselor to evaluate the participant and, if indicated and requested, bring him/her to their facility for emergency residential psychiatric treatment. Drs [name] and [name] will refer questions on the study’s psychiatric emergency cases or protocol to the project’s psychiatrist, [name] (Co-PI), who will be on call for psychiatric issues and emergencies. [name], has developed the mental health crisis protocols for the Lighthouse. All project facilitators and interviewers have received mental health crisis training.

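### The RCT exclusion for severe depression is printed with an inequality that contradicts its own label, the stated target population and the planning mean

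*Protocol*

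**What the plan says.** The protocol sets RCT eligibility in the second tier of Inclusion and Exclusion Criteria (Phase 3: Full Trial), assessed during the baseline survey.

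- RCT inclusion criterion 2: "Have depressive symptoms as determined by CESD scores 16 or greater at baseline assessment".
- RCT exclusion criterion 1: "Severe levels of depression as determined by CESD score ≤40".

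Three other places describe whom the trial is for, or what scores it expects:

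- Research Question: the intervention addresses "HIV risk behaviors among mildly to moderately depressed drug users".
- Rationale: "The proposed intervention will target individuals who have mild to moderate levels of depressive symptoms".
- Power calculations: "we would expect an average CES-D score of 26.7 and variance of 8.3, given the selection methods proposed in the present study".

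The Population section summarises recruitment to the RCT as "approximately 250 crack smokers and 250 injectors with CES-D scores ≥16 will be randomly assigned". It mentions none of the RCT exclusions. No other section states a cut for severe depression.

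**The concern.** The label and the operator in the exclusion criterion point in opposite directions. The inclusion criterion treats higher CES-D scores as more depressive symptoms, so a score of 40 or less cannot be what marks severe depression. As printed, the rule excludes the lower part of the scale and keeps the top.

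This is the operative rule for who may be randomised. If it is followed to the letter, the trial enrols a population that its own rationale does not describe and that its power calculation did not assume. If it is not followed, eligibility is decided by a rule that the protocol does not contain.

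**Working it through.** **Inputs**

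- Inclusion: CES-D ≥16 (RCT inclusion criterion 2).
- Exclusion as printed: CES-D ≤40 (RCT exclusion criterion 1).
- Expected mean 26.7, with a stated variance of 8.3 (Power calculations).
- About 1000 people in the longitudinal cohort (500 + 500) and about 500 randomised (250 + 250) (Population).
- Assumption: scores are whole numbers, so above 40 means 41 or more.

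The mean of 26.7 is taken from a prior study and cannot be derived from the protocol. There is therefore no figure to reproduce, and the check is one of consistency.

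**Step 1. Combine the two criteria.**

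{≥16} and not {≤40} = {>40}.

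All scores from 16 to 40 are ineligible. The ≥16 inclusion rule becomes redundant, because anyone above 40 already meets it.

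**Step 2. Compare with the planning mean.**

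If every randomised score is at least 41, the mean is at least 41. The protocol expects 26.7 under its own selection methods. The two cannot both hold, and this needs no assumption about the distribution. If the operator instead removed high scores, the eligible range would run from 16 to about 40 and 26.7 would lie inside it.

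**Step 3. Bound how many could qualify under the printed rule.**

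The protocol does not say exactly which group the mean describes. Suppose that 26.7 is the mean among people scoring 16 or more, and let p be the share scoring 41 or more. Everyone else scores at least 16, so

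26.7 ≥ 16(1 − p) + 41p, which gives p ≤ (26.7 − 16)/(41 − 16) = 10.7/25 = 0.428.

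Even if all of the roughly 1000 cohort members scored at least 16, at most 0.428 × 1000 = 428 could be randomised, fewer than the planned 500. If 26.7 instead describes a sample already capped near 40, it contradicts the printed rule directly.

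**Step 4. Illustration under an assumed normal distribution with mean 26.7.**

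- Reading 8.3 as an SD: z = (40 − 26.7)/8.3 = 1.60, so about 5.5% lie above 40, or 4.8% with a 0.5 continuity correction. Conditional on scoring at least 16, the corrected share is about 5.3%, and 0.053 × 500 ≈ 26 people.
- Reading 8.3 as a variance, as printed: SD = √8.3 = 2.88, z = 13.3/2.88 = 4.62, and about 0.0002% lie above 40.

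The normal shape and the reading of 8.3 are assumptions. Steps 1 and 2 depend on neither.

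**The case against.** The strongest reply is that this is a slip of one sign and that the intent can be recovered. The criterion names what it excludes, two sections state a mild-to-moderate target, the planning mean fits that target, and the literal reading makes the inclusion cut redundant. The wrong population would be randomised only if someone applied the sign and ignored the words beside it. This largely stands: the harm is conditional, and nothing in the protocol shows that anyone was or would be wrongly enrolled. It does not remove the point. The operative list is the only statement of the threshold, and a reader who sees the reversal still cannot tell whether a score of exactly 40 is in or out.

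A reader might also infer more than the protocol supports:

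- **That the Population section defines a rival RCT population with no upper limit.** It is a short recruitment summary that leaves out every RCT exclusion, including the psychiatric ones. Omitting exclusions from a summary does not set a competing rule.
- **That people scoring above 40 are those sent to crisis services.** Methods for Dealing with Adverse Events says "Individuals who report very high levels of depressive symptoms will be referred to the BCRI". It gives no score, is not tied to 40, and does not say that referral bars anyone from the RCT. A safety consequence cannot rest on it.
- **That different screeners would apply different cuts.** Under Baseline interview, RCT eligibility comes from responses to survey items and not from the brief screener. Nothing suggests that individual staff choose a threshold.

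Finally, the protocol gives no CES-D range for mild to moderate. To say that the printed rule removes exactly that group relies on the criterion's own link between severe and 40.

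**Conclusion.** The point holds as an internal contradiction in the operative eligibility text. As printed, only scores above 40 can be randomised. This conflicts with the criterion's own label, with the target population in the Research Question and Rationale, and with the expected mean of 26.7. The conflict with the mean follows from logic alone. The shortfall against about 500 randomised (at most 428) further assumes that 26.7 is the mean among people scoring 16 or more and that scores are whole numbers. The figure of about 26 per 500 is illustrative only.

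The cause is very probably a reversed sign, and the sign should be confirmed in the signed protocol. The defect concerns RCT eligibility and leaves entry to the longitudinal cohort untouched. It must be corrected, because it is a decision threshold for randomisation that no other passage puts right.

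**What to change.** The sponsor should reconcile RCT exclusion criterion 1 with the Research Question, the Rationale and the mean under Power calculations, so that the operator agrees with the criterion's label and the stated target population. The amended text should say whether a score of exactly 40 is eligible. The sponsor should also confirm that the eligibility logic in the baseline survey matches it. The Population section may cross-refer to the corrected criteria. The choice of cut-off remains with the sponsor; none is proposed here.

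The cost is a short protocol amendment and one check of the survey logic. Neither the design nor the sample size needs to change on this account.

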**Gender, Age and Locale**

**Phase 3: Full Trial**

[name], both males and females will be recruited for the study. All participants will be adults (i.e., 18-55 years).

**Procedures:**

**Recruitment Process**

**Phase 3: Full Trial**

Potential participants will be recruited through outreach, referrals from local agencies, and print advertisements. Trained outreach workers will conduct targeted street outreach in regions of the city that have high levels of drug activity. Recruiters will approach individuals and provide a brief description of the study and give a recruitment flyer and inform interested people to call or visit the Lighthouse to learn more about the study. Posted advertisements displayed at the Lighthouse and other community-based agencies will be used to recruit participants. If needed, we will also place an advertisement in local newspapers. (see attached recruitment flyer)

**Study Procedures in Sequential Order**

**Phase 3: Full Trial**

***Screening***

Individuals who are interested in the study will be screened over the telephone or face-to-face by a trained interviewer in a private office. They will provide verbal consent prior to being administered a brief screening assessment to determine eligibility into the study (see attached screener).

***Baseline interview***

Eligible participants will be sent a Baseline appt reminder letter (see attached letter). Partiicpants who miss their baseline visit will be sent a Missed appointment letter (see attached letter).

Participants will be asked to complete a baseline visit in a private office at the Lighthouse. The baseline visit may take up to 2 ½ hours to complete. After the participant has provided written consent, the baseline visit will begin and consist of the following components:

1) Collection of Locating information: Participants will be asked for information that will be used to try to remain in contact with them to remind about program sessions and follow-up visits. Participants will be asked to provide their names, date of birth, addresses, and telephone numbers. In addition, participants will be asked to provide contact information of at least one person if they are unable to provide their own contact information (e.g., homeless, transient populations). We will try to get as much other locator information as possible for each participant. However, we will not press for additional information if the participant is uncomfortable or distrusting of our motives. Participants will be asked if they are interested in being contacted after the end of the study about future studies. Information will be entered into a Client Locating and Scheduling Database which is a separate database from the survey data. Electronic contact information for participants who do not wish to be contacted in the future will be destroyed 1 year after the study ends by the Data Manager.

2) Survey Administration: A survey will be administered in part by a trained interviewer and a portion will be administered using Audio Computer Administered Self Interview (ACASI) software. Prior to the start of the ACASI portion, the interviewer will show participants how to use the computer and offer assistance if needed.

The survey will include questions on several domains including HIV risk behaviors, physical and mental health history, neighborhood characteristics and drug history. The survey will also include a social network inventory. A network inventory is a commonly used instrument that is used to measure social support and social integration, and diffusion of health information. A modified version of Barrera’s support network questionnaire will be utilized (Barrera, et al., 1981). Participants will be asked to use first names and last initials, nicknames, or initials of those they name in order to keep clear who they are talking about during the questionnaire yet minimize identifiable information. See attached survey. The survey items will also assess eligibility into the RCT. Participants will also be notified of their eligibility for randomization (based on responses to survey items) during the baseline survey.

The survey administration component of the visit will be audio-recorded so that we can conduct quality assurance of the data and ensure that interviewers are following the standard protocols. The audio file will be saved in mp3 format and saved to a password-protected computer. The audio file will be labeled with the study ID of the participant and the type of survey (e.g. 3001baseline.mp3)

4) Testing for Opiate and Cocaine Metabolite: Participants will be asked to provide an oral specimen to test for cocaine and opiate metabolites using the Intercept Oral Collection Device. The purpose of testing for these drugs is to validate drug use measures from multiple sources such as self-reported disclosure. The specimen will be collected using a cotton swab that the participant places in their mouth for 3-5 minutes. The participant’s name will not appear on the specimen or any transmittal forms. Participants will also be informed that refusal to take the test will not affect their participation in the study. Results of this test will not be provided to the participants. The specimen will not be stored and will be destroyed after analysis.

5) Testing for HIV: Participants will also be asked to provide an oral specimen to test for HIV. The purpose of conducting the HIV antibody test is to measure HIV status. Participants from prior studies have also identified testing as a valuable service and benefit to their participation. Participants will be tested for HIV antibody using the OraQuick Advance oral specimen collection device. State and Federal licensure has been obtained to conduct “rapid” HIV testing at the Lighthouse.

Study staff who will be collecting the specimens and providing prevention counseling have received training by the OraSure Technologies Company and the Maryland State AIDS Administration. Following completion of the survey, the participant will receive counseling and complete the OraQuick Advance test. Participants will have the OraQuick oral fluid rapid HIV test administered consistent with instructions included in the test packaging. This is a CLIA-waived test and includes 2 steps before reading a result . For each participant, an oral fluid specimen will be obtained from the mouth using the OraSure oral specimen collection device by swabbing the upper and lower outer gums. The device will then be inserted and stirred into the OraQuick developer solution and vial. Next, the OraQuick test indicator will be inserted into the vial. Typically, test results will be available within 20-40 minutes. During this period, participants will receive prevention counseling in accordance with study protocols. After the result is read, the specimen will not be stored and will be properly disposed at the clinic.

Participants whose result is negative will be notified of their negative test result and will receive prevention counseling. Participants whose test result is reactive will be informed of their preliminary positive test result and will receive prevention counseling. Participants who are learning for the first that time that they may be HIV positive (preliminary positive) will be asked to consent to have 6 cc’s (1 teaspoon) of blood drawn from their arm by a trained phlebotomist to be sent to a lab at the Maryland Department of Health and Mental Hygiene for confirmatory testing. After testing, the blood specimen will not be stored and will be destroyed by the testing lab. The result of a Western Blot test performed on this sample will serve as confirmation of their HIV status and are available in approximately 7 days. Participants will be scheduled to return for the result of this test approximately 7 days after the enrollment visit (depending on local lab schedule). If this confirmatory test is positive participants will be referred to appropriate counseling and medical services.

All participants both those who test HIV positive and negative are eligible to take part in the study. The Lighthouse has a comprehensive resource guide that includes agencies that provide services ranging from healthcare, drug treatment, and housing. Some agencies listed in the compendium are the JHU Moore Clinic, Baltimore City Health Department, and Healthcare for the Homeless.

Through permission of the Maryland State AIDS Administration researchers are provided with exemption from reporting HIV test results pursuant to COMAR 10.18.02.02. One requirement for the exemption is local IRB approval of the project. After receiving JHSPH IRB approval, an application for exemption will be submitted. Exemptions for other studies conducted at the Lighthouse have been received (most recently Unity in Diversity, IRB# 559). Despite this exemption, the number of individuals tested for HIV and the number tested positive are required to be provided to the AIDS Administration These reporting dates are dictated by the AIDS Administration.

